### Intervention

The study has a participant time commitment of 9 months, which includes 1 month of normal activities and management to establish baseline values for outcome measures, followed by 6 months of parkrun participation, and then a follow up at 2 months post-intervention. During the 6 months of parkrun, participants can complete events at their discretion. Parkrun events occur each Saturday morning but we anticipate that many participants may not be able to join in on a weekly basis due to cancer treatment cycles, symptoms, family or work commitments or poor weather. Parkrun events start at approximately 7am, and participants can walk or jog at their own pace. There is no set finish time but the events are normally completed within 2 h, allowing social gathering time afterwards.Volunteer marshals are stationed every few hundred metres along the paths to assist with directions, encouragement and for participant safety. Each participant wears their individual barcode so that their finish time is recorded electronically, captured and stored by the parkrun organisation. Individual results can be accessed by each participant.Volunteers have first aid and CPR training.Each course will have a first aid kit and automated defibrillator available and access for emergency vehicles if necessary.In the case of bad weather, an event would be cancelled.

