### Statistical analyses, sample size and power calculation

Numerical data from demographic, physical and scored questionnaire outcome measures will be analysed using Excel spreadsheets, IBM©SPSS version 29 and R studio [35]. Qualitative data (mood, participant feedback survey responses, participants’ attitudes towards the intervention, enjoyment, appropriateness, suitability, convenience and perceived effectiveness of the intervention) will be analysed thematically using NVivo and following the process of Braun and Clarke (2006) [36]. Comments will be read, organised and coded using an iterative framework (familiarisation; generation of initial codes; search for themes; review of themes; definition of themes and a final report). The codes will be reviewed, discussed and refined with the coding framework drawn from the data as well as being informed by the survey questions and themes highlighted in wider literature on parkrun outcomes [19, 20]. 

Participant demographic and cancer-related variables will be summarised using descriptive statistics (e.g. count or percent; mean and standard deviation). Linear mixed effect models will be used to determine the effect of parkrun participation on the proportion of participants meeting minimal PA recommendations. These models will include a random intercept for each participant, to account for the clustering of observation on each individual (i.e. measurements at baseline, 4-weeks usual activities, following 6 months of parkrun participation, and 2-month follow-up). A histogram and quantile-quantile plot of the model residuals will be used to determine whether the assumption of normally distributed errors is met. Model fit will be assessed using the adjusted R^2^ value and the model residual standard error; the most parsimonious model will be selected for inferences. Effect sizes (Cohen’s d) will be calculated where there are significant effects of time using the pooled standard deviation as the denominator.

In the case of participant attrition from the study, or if participants miss parkrun events in the 6-month intervention period, researchers will follow up with each participant individually, either through the study or at the end of the study. Reasons for reduced attendance or attrition can be gained from the participant and this information is valuable for informing the researchers of potential barriers or issues with parkrun as a mode of cancer rehabilitation exercise.

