Sample size was determined via simulation methods using a random intercept model with the R package [35]. We were interested in powering the study to detect changes in exercise adherence (measured as the proportion of cancer patients meeting minimum physical activity guidelines) and used this outcome variable in simulations. Data used to create the model were informed by previous studies [8, 10]. We assumed the average proportion of cancer patients meeting minimal physical activity guidelines for aerobic exercise was 30% [37]. Time (three levels- baseline, 6-months parkrun and follow-up), body mass index (BMI) and sex (two levels- male and female) were included as fixed factors within the sample size model. A random intercept was included for each individual participant. BMI and sex were included as fixed factors as these variables can influence exercise adherence in cancer patients [8–10]. Calculations were made assuming fixed effects of 6%, 30% and 5% for sex, time and BMI respectively, and a standard deviation of the random intercept of 2%. Based on these assumptions and a type I error rate of 5%, 80 participants give approximately 80% power to detect the specific time effect of 30% increase in the proportion of participants meeting physical activity recommendations. A minimum of 100 participants will be recruited, which even allowing for potential attrition of 20 participants would still provide a minimum sample size of 80.

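### The only within-person term named is a random intercept, which imposes equal correlation on visits at 0, 1, 7 and 9 months; if correlation falls with time, contrast standard errors err in both directions

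*Protocol article*

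**What the plan says.** The section on statistical analyses, sample size and power calculation plans linear mixed models to estimate "the effect of parkrun participation on the proportion of participants meeting minimal PA recommendations". On repeated measures it says: "These models will include a random intercept for each participant, to account for the clustering of observation on each individual". The observations meant are "measurements at baseline, 4-weeks usual activities, following 6 months of parkrun participation, and 2-month follow-up".

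The Intervention section fixes the spacing as "1 month of normal activities and management to establish baseline values for outcome measures, followed by 6 months of parkrun participation". The last visit comes two months after that block ends. T1 to T4 therefore fall at 0, 1, 7 and 9 months.

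The model checks are a histogram and Q-Q plot of residuals, adjusted R-squared and the residual standard error, after which "the most parsimonious model will be selected for inferences". The sample-size simulation also uses a random-intercept model. The article mentions no random slope, residual correlation structure or robust variance, and it gives no between-visit correlation. It does not say that the intercept is the only within-person term.

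**The concern.** A random intercept with independent residuals makes two measurements one month apart exactly as alike as two measurements nine months apart. With complete data every pairwise time contrast then gets the same SE, based on the average correlation.

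Falling correlation is plausible in this population. Participants may be on treatment or in remission, and clinically stable or unstable. Six months of discretionary parkrun attendance also separates T2 from T3. If correlation does fall, a shared SE is too large for neighbouring visits and too small for distant ones.

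This matters because there is no comparator group. The T1-T2 block is the only control period, and its contrast is the most distorted: real drift before parkrun could go undetected. The third hypothesis under Study objectives compares with baseline, so T3-T1 and T4-T1 are natural contrasts, and these would be tested slightly too liberally. None of the listed checks looks at correlation between visits.

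**Working it through.** **The plan's own figures.** The plan gives no SE or correlation for any time contrast. Its one within-person figure is a random-intercept SD of 2%. With 30% meeting guidelines, the yes/no variance is 0.30 × 0.70 = 0.21, so the implied intraclass correlation is 0.02² / 0.21 = 0.0004 / 0.21 ≈ 0.002. That is practically independent visits; simulated SE ratios in that case were 0.95 to 1.03. The stated 80% power is not an input here.

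**Inputs.** Visit times 0, 1, 7 and 9 months (Intervention section). Assumed, because the documents give nothing: the correlations, equal variances across visits, and complete data.

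**Formulas.** Let ρ_jk be the true correlation between visits j and k, and ρ̄ the mean over the six pairs.
- Model variance of any pairwise contrast ∝ 2(1 − ρ̄); true variance ∝ 2(1 − ρ_jk).
- Model SE / true SE = √[(1 − ρ̄)/(1 − ρ_jk)].
- True size of a nominal 5% test = 2[1 − Φ(1.96 × ratio)].
- For (T3−T2)−(T2−T1) = T3 − 2·T2 + T1: model variance 6(1 − ρ̄); true variance 6 − 4ρ12 − 4ρ23 + 2ρ13.

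**Two assumed patterns.** Geometric decay through the two end values, ρ(d) = ρ(1) × [ρ(9)/ρ(1)]^((d−1)/8), where d is the lag in months. Mild: 0.67 falling to 0.53, ρ̄ = 0.590. Strong: 0.79 falling to 0.44, ρ̄ = 0.583.

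| Contrast | Lag (months) | Mild: ρ, ratio, size | Strong: ρ, ratio, size |
|---|---|---|---|
| T2-T1 | 1 | 0.670, 1.12, 2.9% | 0.790, 1.41, 0.6% |
| T4-T3 | 2 | 0.651, 1.08, 3.4% | 0.734, 1.25, 1.4% |
| T3-T2 | 6 | 0.579, 0.99, 5.3% | 0.548, 0.96, 6.0% |
| T3-T1 | 7 | 0.562, 0.97, 5.8% | 0.509, 0.92, 7.1% |
| T4-T2 | 8 | 0.546, 0.95, 6.2% | 0.473, 0.89, 8.1% |
| T4-T1 | 9 | 0.530, 0.93, 6.7% | 0.440, 0.86, 9.1% |

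Example, T2-T1, strong: √[(1 − 0.5825)/(1 − 0.79)] = √(0.4175/0.21) = 1.41.

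**Difference of changes.**
- Mild: true 6 − 2.680 − 2.315 + 1.124 = 2.129; model 6 × 0.4105 = 2.463; ratio √(2.463/2.129) = 1.08, size 3.5%.
- Strong: true 6 − 3.160 − 2.192 + 1.019 = 1.667; model 6 × 0.4175 = 2.505; ratio 1.23, size 1.6%.

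**Equal correlation.** With ρ = 0.5 for every pair, every ratio is 1.00 and every size 5.0%.

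**Yes/no outcome.** In simulations with n = 80 under comparable assumed decay, the T2-T1 SE was 6% to 24% too large and the T4-T1 size 6% to 8%; paired SEs gave about 4% to 6%.

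**Wider range.** Continuous decay with no visit-level noise is an extreme case. It gave T2-T1 ratios of 1.86 to 2.26 and T4-T1 sizes of 9.9% to 12.1%. Across the latent-decay patterns tried for the yes/no outcome, the T3-T2 error rate ran from 5.2% to 8.5%.

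Physical function is measured only at T1 to T3, so these four-visit figures do not describe it.

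**The case against.** The strongest reply is that no error has been shown. The documents give no between-visit correlation, equal correlation would make the SEs right, and the plan's own 2% intercept SD implies almost no correlation at all. This stands, and the point is conditional for that reason. A reader might infer that the SEs are certainly wrong; the documents do not support that.

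Next, saying that models include a random intercept does not exclude further terms, and a condensed article may leave covariance detail to a fuller document. This stands in part. The article does, however, name the intercept as its means of handling clustering, uses the same structure for sample size, and prefers the most parsimonious model. Read as written, it leads to equal correlation.

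A reader might also infer that the distortion favours parkrun throughout. It does not. A conservative control-month test beside liberal baseline-to-later tests could flatter parkrun only if the two significance results were set against each other, and the protocol states no such rule. The contrast that compares the two changes directly has an SE that is too large, so it works against finding an effect. T3-T2 is barely affected.

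Finally, the primary objectives are acceptability and adherence, which these time contrasts do not estimate. That limits the weight of the point but does not remove it.

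**Conclusion.** The point holds conditionally. As written, the model gives every time contrast the same SE despite lags of 1 to 9 months. If correlation falls from about 0.66-0.79 at 1 month to 0.44-0.53 at 9 months:
- the control-month change (T2-T1) is tested too conservatively, with an SE about 12% to 41% too large (6% to 24% for the yes/no outcome);
- T3-T2 is close to correct, with an SE 1% to 4% too small and size about 5% to 6%;
- T4-T1 is somewhat liberal, with size about 6% to 9%; T3-T1 and T4-T2 err the same way but less;
- (T3-T2)-(T2-T1) loses power, with an SE about 8% to 23% too large.

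These sizes rest on assumed correlations, complete data and equal variances. Under equal correlation they vanish. This is a modest weakness in the inference on secondary time contrasts, worth correcting because the correction is valid in either case.

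**What to change.** Keep the time model, and state that SEs for all time contrasts will be participant-clustered robust (sandwich) SEs. For continuous outcomes, an unstructured within-person covariance is an alternative. For the yes/no guideline outcome, use GEE with robust SEs. Name the contrasts to be reported: T2-T1, T3-T2, T4-T2 and, if the control and intervention changes are to be compared, (T3-T2)-(T2-T1).

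The cost is about one line of wording. Robust SEs may need a small-sample correction with 80 to 100 participants. An unstructured covariance over four visits has ten parameters (4 variances and 6 covariances), which that number can support. No extra data or visits are needed.

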**Methods:**

This protocol describes a single-arm intervention study with participants acting as their own controls. The study accepts adults diagnosed with any type of cancer, undergoing treatment or in remission. Participants must be able to walk and have medical clearance to exercise. A sample of 100 participants will be recruited across the Sunshine Coast over two years. Data will be collected over 9-months at 4 time points: Baseline (T1); after 4-weeks of usual daily activities and cancer management prior to parkrun participation(T2); after a 6-month parkrun intervention (T3); at 2-month follow-up (T4). The primary objectives are to assess the acceptability of, and adherence to, parkrun as rehabilitation exercise. Secondary outcomes include wellness, health-related quality of life, anxiety, depression, mood, physical function, parkrun metrics, dietary intake, and diet and exercise behaviour.

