**Assessments / Tools**							
Demographics & Clinical Characteristics			X				
Physical Function (Resting HR, BP, O2sat, 6MWT, 30-s Sit-to-Stand)			X	X	X		
Health-related Quality of Life (EORTC QLQ-30) questionnaire			X	X	X	X	
Anxiety & Depression (HADS) questionnaire			X	X	X	X	
General Physical Activity (IPAQ-SF)			X	X	X	X	
Dietary Intake (MEDAS) questionnaire			X	X	X	X	
Mood (Daylio app)			X	X	X	X	
Sleep Quality (Daylio app)			X	X	X	X	
Participant Satisfaction, Diet, Exercise behaviour, Intent Feedback Surveys					X	X	
Parkrun event Adherence					X	X	
INTERVENTIONS:							
Parkrun participation					X		

This protocol describes a single group cohort study with participants acting as their own controls [23]. The study outline and timeline is shown in Fig. 1.

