## Outcomes

### Study objectives

This feasibility study has been developed primarily to assess the acceptability of, and adherence to, parkrun as an enjoyable exercise intervention for cancer survivors. Secondary aims are to assess the efficacy of parkrun to improve social support, HRQoL, mental health, to prevent physical and functional decline [3, 4, 26] as well as influence dietary intake [26–28]. 

We hypothesised that:

Consistent parkrun participation will improve cancer survivor engagement in physical activity, social interaction and social identity.Cancer survivors will enjoy doing parkrun events.Parkrun participants will have improved physical function, HRQoL, mental health, disease symptoms and treatment side-effects compared to baseline measures.Parkrun participation may indirectly affect the dietary intake of cancer survivors.

Outcome measures will be assessed at enrolment and initial screening [25] (baseline, T1); after 4 weeks of usual management and activities of daily living (ADL, T2); after 6 months of parkrun participation (T3); 2 months post-intervention follow-up (T4) (Fig. 1).

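### The study's only control is the four-week block before parkrun (T1 to T2), but the stated comparisons run from T1 or refer to time in general, so change in that block would be counted in the secondary efficacy claims for parkrun

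*Protocol article*

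**What the plan says.** Experimental design calls the trial a "single group cohort study with participants acting as their own controls". Table 1 labels the four-week T2 visit as the control block, and the abstract places T2 "after 4-weeks of usual daily activities and cancer management prior to parkrun participation(T2".

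Four statements then bear on how that block is used:

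- **Study objectives** attaches the word baseline to T1 and lists T2 separately: "baseline, T1); after 4 weeks of usual management and activities of daily living (ADL, T2". Hypothesis 3 reads: "Parkrun participants will have improved physical function, HRQoL, mental health, disease symptoms and treatment side-effects compared to baseline measures".
- **Intervention** gives the block a different purpose: "1 month of normal activities and management to establish baseline values for outcome measures".
- **Statistical analyses** applies linear mixed models, with a random intercept per participant, to the proportion meeting physical activity recommendations. The modelled visits are "measurements at baseline, 4-weeks usual activities, following 6 months of parkrun participation, and 2-month follow-up". Cohen's d follows where time is significant. No pair of visits is named as the parkrun comparison.
- **Sample size**, in the same section, uses a model with "Time (three levels- baseline, 6-months parkrun and follow-up", so T2 is absent.

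**The concern.** In a single-arm study the own-control claim rests on the pre-intervention block. Whatever happens between T1 and T2 cannot be due to parkrun, because parkrun starts after T2. The protocol itself shows ways in which values could move in that month: the six-minute walk and sit-to-stand tests are repeated, participants keep a daily mood and sleep diary, and some are under treatment.

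If the reported effect is T3 minus T1, it is the sum of the control-block change (T2 minus T1) and the change over the parkrun period (T3 minus T2). A rise in the first part would be credited to parkrun, and a fall would hide part of any benefit. The claims at stake are those for physical activity, quality of life, mental health and physical function. They are secondary aims, although physical activity is also the outcome on which the study was sized.

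**Working it through.** **Inputs from the article.** 80 participants analysed; 30% meeting guidelines at the start; type I error 5% (taken as two-sided, since sidedness is not stated); random-intercept SD 2%; four visits in the analysis model and three in the sample-size model.

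**Assumed.** The T1-T2 change, for which the documents give no value. Rises of 5 to 20 percentage points are examined, sustained through T3 and T4, with no parkrun effect.

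**The plan's own figure.** The article states about 80% power with 80 participants for a 30% increase. Simulating the three-level model without BMI and sex, whose scaling is not given, yields about 97-99% if the increase is absolute (30% to 60%) and about 21-24% if it is relative (30% to 39%). The stated figure is not reproduced. Because the inputs are incomplete, it is unconfirmed rather than shown wrong, and nothing below depends on it.

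**Step 1: split the comparison.** (T3 − T1) = (T2 − T1) + (T3 − T2). With no parkrun effect the last term is zero on average, so T3 − T1 estimates the whole control-block change.

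**Step 2: how often it would be significant.** With a random-intercept SD as small as 2%, the visits are nearly independent. Let v be the mean of p(1 − p) over the four visits. Then SE = √(2v/80), z = d/SE, and the chance of significance is Φ(z − 1.96) + Φ(−z − 1.96).

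For d = 0.15 the proportions are 0.30, 0.45, 0.45, 0.45:
- v = (0.21 + 3 × 0.2475)/4 = 0.2381
- SE = √(2 × 0.2381/80) = 0.0772
- z = 0.15/0.0772 = 1.94, which gives 49%

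| T1-T2 rise, no parkrun effect | v | SE | z | T3 vs T1, formula | T3 vs T1, simulated | T3 vs T2, simulated |
|---|---|---|---|---|---|---|
| 5 points | 0.2231 | 0.0747 | 0.67 | 10% | 9-11% | about 5% |
| 10 points | 0.2325 | 0.0762 | 1.31 | 26% | 24-26% | 5-6% |
| 15 points | 0.2381 | 0.0772 | 1.94 | 49% | 48-49% | about 5% |
| 20 points | 0.2400 | 0.0775 | 2.58 | 73% | 72-73% | about 5% |

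An overall test of time across the four visits behaves much like T3 versus T1: about 9-10%, 24%, 48-49% and 76%. With a random-intercept SD of 20% the pattern holds: T3 versus T1 is significant in about 10%, 27%, 53% and 78%, and T3 versus T2 in about 5-7%.

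**Step 3: consequence for power.** Suppose a 30-point rise from T1 to T3 is 15 points before T2 and 15 after, so the proportions are 0.30, 0.45, 0.60, 0.60. Then v = 0.2344 and SE = 0.0765. T3 versus T1 has z = 3.92 and power of about 97%. T3 versus T2 has z = 1.96 and power of about 50% (49% simulated). If T2 equals T1, the two comparisons have essentially the same power.

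**The case against.** The strongest reply is that T2 is in the analysis model as a visit of its own, so T3 minus T2 can be read straight from it, and an article may leave the choice of contrast to a fuller plan. The first part stands. A reader might infer that the control block is collected and then ignored, or pooled away, and the text does not support that. The second part stands only in part. The point does not rest on silence, because the article does state a comparator (baseline, defined as T1) and a power model without T2. A separate plan that named T3 minus T2 would conflict with both.

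A reader might also infer that an overall test of time is the declared basis for efficacy claims. The article does not say so. Significance of time appears only as the trigger for reporting Cohen's d, and the mixed model is described only for the physical activity proportion. The comparison with baseline belongs to hypothesis 3, which covers the other outcomes. So the problem arises by two routes and is not one stated test applied to everything.

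The purpose given under Intervention could make T1 and T2 jointly the baseline. That reading is possible, but Study objectives contradicts it, so the two sections need reconciling.

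Finally, nothing in the documents shows that values will move between T1 and T2. That is correct. Nor is a significant T3-T1 difference in these scenarios a type I error of that test, because T1 really does differ. The error lies in crediting the difference to parkrun.

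**Conclusion.** The concern holds as a should-fix. The own-control design has one control period, and the article's stated comparator and sample-size model both bypass it, while the analysis text names no comparison that isolates the parkrun period. T3 versus T1 carries the full T1-T2 change into the claimed effect. For 80 participants and no parkrun effect, the chance of a significant result runs from about 10% for a 5-point rise to about 73% for a 20-point rise, against about 5% for T3 versus T2. These figures rest on the assumed rise, on its being sustained, and on the 30% starting proportion. They illustrate physical activity only and do not forecast drift.

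It would be too strong to say that this undermines the study's main purpose. The primary objectives are acceptability and adherence, and adherence is events attended divided by events available, which uses neither T1 nor T2. Limitations also acknowledges the lack of randomisation.

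**What to change.** - Name T3 minus T2, from the existing mixed model, as the parkrun comparison. Report T2 minus T1 beside it as the control-block change, and T4 minus T3 where measured (physical function stops at T3).
- Reword hypothesis 3 to compare with T2.
- Reconcile Intervention and Study objectives on what baseline means.
- Use the same time levels, including T2, in the sample-size paragraph, and rerun the simulation.
- State that T3 minus T2 does not remove natural change over the six months, and that a four-week block is only a limited guide to it.

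The cost is wording plus a rerun of the power simulation, with no new data. The claimed effect may be smaller than T3 versus T1, and its power lower if part of the change comes before T2. The article reports that no data had been collected, so the comparison can be fixed before any result is known.

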### Limitations

The study has several strengths and limitations. Advantages include the use of an existing exercise program that has no direct costs, is easily accessible, is outdoors, and is supportive and safe in nature. The study will comprehensively profile participants and will have quantitative and qualitative outcome measures, participants’ experiential data and follow-up surveys. Limitations include the lack of randomisation and inclusion of participants with different types and stages of cancers. However, using a heterogenous sample is useful from the perspective of real-world clinical practice. As a feasibility study, this trial aims to identify benefits and barriers that affect parkrun participation and participant enjoyment and acceptance, and to lead to a larger longitudinal study.

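### Cohen's d is to be calculated only after a significant time effect, so the reported standardised effects are selected and biased away from zero (minor)

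*Protocol article*

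**What the plan says.** Under Statistical analyses, sample size and power calculation, the protocol article plans linear mixed models with a random intercept per participant. It then says that Cohen's d "will be calculated where there are significant effects of time using the pooled standard deviation as the denominator". No other sentence in the article calls for an effect size where time is not significant.

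The same section powers one outcome, the proportion meeting minimum physical activity guidelines: "We were interested in powering the study to detect changes in exercise adherence". It states that "a type I error rate of 5%, 80 participants give approximately 80% power to detect the specific time effect of 30% increase" in that proportion. No power is given for any other outcome.

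Study objectives makes acceptability and adherence primary. Efficacy on social support, HRQoL, mental health, physical and functional decline, and diet is secondary. Limitations adds that the study aims "to lead to a larger longitudinal study".

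**The concern.** An estimate that is calculated only when its test is significant has passed through a filter. Small observed effects are dropped and large ones kept, so the average reported value lies further from zero than the truth. The lower the power, the stronger the filter. The outcomes most exposed are the secondary ones, for which the article states no power.

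The rule also fits one secondary aim badly. Where the hope is to prevent physical and functional decline, a flat result can be the favourable one. Under the rule that result carries no effect size. An estimate with an interval would show how much decline the data still allow.

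At stake is the record of standardised effects on the secondary outcomes, and anything that later readers build on it.

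**Working it through.** **The plan's own figures.** The recruitment target follows from the stated attrition: 80 / (1 − 0.20) = 100. The 80% power could not be reproduced, because the article does not give the residual SD, the BMI scale, or whether the 30% increase is absolute or relative. An absolute rise from 30% to 60% gives 97.4% by the two-proportion formula with 80 per time point, and 97% to 99% in a simulated random-intercept model. A relative rise from 30% to 39% gives about 22%. That is a separate matter, and nothing below depends on it.

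**Inputs for the selection check.**
- From the article: n = 80 analysed, type I error 5% (taken as two-sided), Cohen's d with a pooled SD.
- Assumed, because the article does not give them: within-person correlation ρ (range 0.4 to 0.8) and true d.

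**Single contrast between two time points.**
- SE = √(2(1 − ρ)/n). Write δ = d/SE, with critical value c = 1.99.
- Probability of significance: P = Φ(δ − c) + Φ(−δ − c).
- Mean d among significant results: d + SE × [φ(c − δ) − φ(c + δ)] / P.

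Worked case, ρ = 0.6 and d = 0.20: SE = √(0.8/80) = 0.10, δ = 2 and P = 0.504. The mean retained d is 0.20 + 0.10 × (0.3989 − 0.0001)/0.504 = 0.279.

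Mean reported d at n = 80, with the probability of significance in brackets:

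| ρ | true d 0.20 | true d 0.30 | true d 0.50 |
|---|---|---|---|
| 0.4 | 0.327 (36%) | 0.365 (68%) | 0.506 (98%) |
| 0.5 | 0.304 (42%) | 0.346 (76%) | 0.502 (99%) |
| 0.6 | 0.279 (50%) | 0.328 (84%) | 0.500 (>99%) |
| 0.7 | 0.252 (63%) | 0.313 (93%) | 0.500 (>99%) |
| 0.8 | 0.225 (80%) | 0.302 (99%) | 0.500 (>99%) |

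**Overall test of time.** The article conditions on an effect of time, not on one contrast. So four time points were also simulated (n = 80, ρ = 0.5, assumed means 0, 0, d, d/2), with d taken from T1 to T3:

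| true d | mean d, all runs | mean d, significant runs only |
|---|---|---|
| 0.10 | 0.10 | 0.22 |
| 0.20 | 0.20 | 0.29 |
| 0.30 | 0.30 | 0.34 |
| 0.50 | 0.50 | 0.50 |

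The first results column is what the fix delivers, the second what the rule delivers. At n = 100 and ρ = 0.7, true values of 0.20 and 0.30 are reported as 0.23 and 0.31.

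**By power alone (z-test).** The inflation factor is 2.23 at 20% power, 1.80 at 30%, 1.41 at 50%, 1.12 at 80% and 1.03 at 95%.

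**Possible onward effect, illustration only.** Suppose a later two-arm study used d with 80% power and two-sided 5%: n per arm = 2(1.960 + 0.842)²/d². With d = 0.20 this is 393; with d = 0.29 it is 187. If the truth is 0.20, 187 per arm gives power Φ(0.20 × √(187/2) − 1.960) = Φ(−0.026) = 49%.

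**The case against.** Several parts of the case on the other side stand.

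- **The rule restricts one quantity.** A reader might infer that non-significant outcomes are left with no estimate at all. The text does not say so. The mixed model yields a time coefficient and standard error whatever the p-value, and nothing in the article suppresses them. That the article does not promise intervals in its tables is no fault in a condensed article. What is lost is the effect size.
- **The word 'only' is not in the text.** It is the natural reading of the condition, but it is a reading.
- **Use of d for planning is not stated.** A reader might infer that the follow-on study will be sized on these values and so will be too small. Limitations says only that this study should lead to a larger longitudinal one. It does not say what will size that study, or that it will be a two-arm trial. Data management also plans public release of de-identified data and code, from which unselected estimates could be computed.
- **The primary objectives are untouched.** Adherence is a percentage calculated for each participant, with no significance condition, and acceptability comes from the participant survey.
- **The inflation is not one number.** An overstatement of about 40% holds for a true d of 0.20 at moderate correlation. It is about 12% at 80% power and negligible at d = 0.50.
- **The scale of the guideline outcome is a different question.** Cohen's d is an awkward scale for a proportion, but the article does not say which outcomes d will cover. This adds no weight to the selection point. Nor does the choice of time contrasts, which is also separate.

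What the objection does not remove is the rule itself. It is stated in the article, not left open, and it selects the reported standardised effects on significance.

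**Conclusion.** The concern holds as a minor reporting defect. Cohen's d values produced under the stated rule are biased away from zero, and outcomes without a significant time effect receive none.

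At n = 80, a true d of 0.20 would be reported on average as about 0.23 to 0.33 (13% to 64% too large) as the correlation falls from 0.8 to 0.4. A true d of 0.30 would be reported as at most about 0.35 at correlation 0.5 or more, and at d = 0.50 the bias is negligible. These sizes rest on assumed correlations and true effects; only the direction follows from the rule itself.

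If such values were used to plan the larger study, that study could be undersized. The article does not state that use, so this is a conditional risk, not a predicted consequence. No primary feasibility conclusion is affected.

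**What to change.** Delete the clause that makes the calculation of Cohen's d depend on a significant time effect. In its place, state that the estimated change with a 95% CI will be reported for every quantitative outcome and each planned time contrast, whatever the p-value. Add a standardised difference for continuous scores, and use a risk difference with a 95% CI for the proportion meeting physical activity guidelines.

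The cost is one changed sentence and a few more table rows. No new data, test or sample size is needed. The article says that no data had been collected when it was written, so the change could have been made before any result was known.
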